**In-person measurements**						
	Height (m)		✓			
	Weight (lbs)		✓	✓	✓	✓
	Waist circumference (cm)		✓	✓	✓	✓
	Resting heart rate (BPM)		✓	✓	✓	✓
	CRF^i^ (6MWT^j^) [89]		✓	✓	✓	✓

^a^T2D: type 2 diabetes.

^b^ADA: American Diabetes Association.

^c^HbA_1c_: glycated hemoglobin.

^d^GLTEQ: Godin Leisure Time Exercise Questionnaire.

^e^PAV: Physical Activity Vital Sign.

^f^SSBC: Small Steps for Big Changes.

^g^HRQOL: Health Related Quality of Life.

^h^HRU: Health Resource Utilization Questionnaire.

^i^CRF: cardiorespiratory fitness.

^j^6MWT: 6-minute walk test.

#### Objective 2c: Examine the Cost-Effectiveness of SSBC

The cost-effectiveness of SSBC will be determined using organizational data collected in objective 2a and client-level costs. Health-related client-level costs will be detailed using the Health Resource Utilization Questionnaire [88] delivered in a survey. The Health Resource Utilization Questionnaire asks for specific details regarding health professional visits, admissions to the hospital, laboratory tests or investigations, and use of medications. On a per-client basis, costs will be assigned to health care resource use using a fully allocated hospital cost model (for in-patient costs) and provincial guides to medical fees (for outpatient costs) every 6 months to account for potential fluctuations in medical costs. The 5 dimensions of EQ-5D-5L will be converted into a weighted health state utility value that will provide weightings for quality-adjusted life years (QALYs) and Canadian conversion tariffs for transforming health state profiles into utility scores [90]. QALYs are calculated based on the quality of life of a person (measured using health state utility values estimated from the EQ-5D-5L) in a given health state and the time spent in that health state. Incremental cost per client and effects generated by SSBC will be assessed using a Canadian health care system perspective. The outcome of cost-effectiveness analysis is the incremental cost-effectiveness ratio, where incremental cost-effectiveness ratio=Δ Cost/Δ HbA_1c_ and is the incremental cost of SSBC delivery per client. The outcome of our cost-utility analysis is the incremental cost-utility ratio, where incremental cost-utility ratio=Δ Cost/Δ QALY [91].

### Sustainability Phase

#### Objective 3a: Cocreate Sustainability Models

In collaboration with the partnering YMCAs and affiliated municipality partners, the research team will engage in a process of codeveloping a feasible and reciprocally beneficial model of sustaining SSBC within each organization. Data from objectives 1 and 2 will be used to generate reports for each YMCA to directly inform this phase. Next, focus groups will be held at each site. Guided by the Integrated Sustainability Framework (ISF) [44], municipality-level models will establish which program components of SSBC will be continued (if at all), and at what intensity. Focus groups will also elucidate what factors result in the sustainment of evidence-based interventions in community settings. The outcome of this objective will be the development of a logic model of sustainment satisfactory to all parties.

#### Objective 3b: Examine SSBC Sustainability

Sustainability of SSBC will be examined at the individual client level (the number of clients who enroll and complete SSBC in the sustainability phase), individual coach level (the number of coaches that continue to deliver SSBC in the sustainability phase), and the site level (the number of sites that continue SSBC delivery in the sustainability phase; see Table 4). Potential contextual factors that influence the sustainability of SSBC will be explored through interviews with site leads and senior leadership 1 year into the sustainability phase of the project (2028) and at the end of the sustainability phase (2029). Interview guides will be developed using the ISF [44]. In addition, regional research coordinators will document any contextual factors impacting sustainability during regular meetings with site leads. All sustainability determinants will be deductively coded to the categories represented in the ISF (outer context, organizational context, processes, intervention characteristics, and implementer characteristics) by 2 independent coders. Implementation strategies used during this sustainability phase will be documented and analyzed as per the same processes used for implementation.

**Table 4 table4:** Overview of sustainability outcomes and determinants, their operationalization, data sources, and measurement tools. The outcome is sustainability.

Indicators or definition	Data source	Measurement tool and time point
Site level: number of sites continuing delivery, intention to deliver the program, actual delivery of the program, and attempts to seek funds to run the program if appropriate	SL^a^, Y-SL^b^, and RRC^c^	Interviews with SL and Y-SL, focus groups, annual monitoring, and monthly meetings with RRC
Staff level: number of coaches continuing to deliver the program	SL and RRC	Site monthly meetings during the sustainability phase and annual reporting
Individual level: number of clients who participated in the presustainability phase and number who participated in the sustainability phase, if applicable	SL and RRC	Site monthly meetings with RRC and REDCap^d^
Sustainability determinants: contextual factors as assessed through the ISF at 24 months into implementation, after 1 year of sustainability, and end of sustainability	C^e^, SL, Y-SL, MP^f^, PP^g^, and RRC	Interviews, focus groups, and site monthly meetings with RRC
Implementation strategies: strategies continued, discontinued, and reasons	C, SL, Y-SL, MP, PP, and RRC	Interviews, focus groups, and site monthly meetings with RRC

^a^SL: site lead.

^b^Y-SL: Young Men’s Christian Association senior leadership.

^c^RRC: Regional Research Coordinator.

^d^REDCap: Research Electronic Data Capture.

^e^C: coach.

^f^MP: municipality partners.

^g^PP: patient partner.

#### Recruitment and Consent

##### SSBC Clients

Recruitment strategies will vary across delivery sites, based on the local connections previously or newly established by the research team and delivery team. A series of generic recruitment materials (eg, posters, pamphlets, or social media posts) and potential recruitment pathways (eg, health assessment days and physician referrals) have been generated by the research team and will be shared with all delivery sites. These recruitment strategies will be included in the implementation strategies’ blueprint and toolkit. Each site will tailor their recruitment plan to the local contextual needs with support from the research team.

Interested or referred individuals will complete an eligibility survey to determine their eligibility for SSBC. Individuals are eligible for SSBC if they are 18 years of age or older, able to read and speak English, and meet one of the following criteria: (1) have been diagnosed with prediabetes by a physician, (2) have an HbA_1c_ of 5.7%-6.4%, (3) have an American Diabetes Association risk assessment score indicating high risk (≥5), or (4) have achieved T2D remission (have an HbA_1c_ of <6.5%) without any diabetes-related medications for a minimum of 3 months. Eligible individuals will be directed to an online consent form. Following completion, individuals will be scheduled for their first SSBC session at their local YMCA implementation site.

Individuals who express an interest in the substudy will be given a blood requisition form for an HbA_1c_ measurement from a partnering local blood requisition laboratory. The substudy will aim to oversample individuals identifying as visible minority to ensure that priority populations are represented in line with the most recent Canadian Government statistics (based and derived directly from the concept of visible minority in the census [31.3% of the Canadian population identify as being from a racialized group, with 25.2% as visible minority and 6.1% from Indigenous ancestry]). The substudy will also oversample individuals identifying as male, who are at greater risk for having prediabetes and developing T2D [6], yet are disproportionately represented in DPPs [92]. Demographic information of clients enrolling in the substudy will be assessed every 6 months to determine the proportion of individuals self-identifying as visible minorities and males. Purposive sampling may be used during the substudy if the demographic data of subsample clients demonstrates over- or underrepresentation.

##### SSBC Delivery Team

YMCA staff from the delivery sites will be invited to participate in this study to provide feedback on adaptation, implementation processes, and factors influencing implementation and sustainability of SSBC at their site. Site leads and coaches will be identified by senior leadership at each YMCA facility. After completing coach training, site leads and coaches will receive a consent form to participate in surveys, interviews, and focus groups. Senior leadership will receive a consent form 12 months into the program delivery, inviting them to participate in interviews and focus groups.

##### Project Governance

A holacratic approach to organizational operations was codeveloped with delivery sites to enhance conflict resolution and achieve project objectives. Specifically, each team member is considered integral and acknowledges their interconnected role in multiple project processes and outcomes (Figure 4). Municipality partners (made up of patient partners, SSBC alumni, and persons with lived experience) are central to advising the project. The delivery team—the community-dwelling staff who deliver SSBC and liaise directly with researchers, senior YMCA leadership, and municipality partners—will provide ongoing feedback on referral and recruitment strategies, SSBC implementation and adaptations, and factors influencing organizational and staff readiness. YMCA senior management at each site oversees the delivery team and reports to the research team. Three committees will provide feedback and guidance on methods used, analyses performed, outputs reported, and the sustainability plan based on their expertise and experiences for sex, gender, and inclusivity; program evaluation; and the diabetes prevention engagement committee. Finally, an advisory committee will act as an external committee distinct from the project team. This committee will ensure that safe and ethical principles are applied throughout the project, project milestones are met promptly, and all decisions are made with clients and delivery organizations in mind.

**Figure 4 figure4:**
[figure not shown]
Project governance model. SSBC: Small Steps for Big Changes; YMCA: Young Men’s Christian Association.

### Ethical Considerations

This study has been approved by the University of British Columbia Clinical Research Ethics Board (H23-01930) and other university and provincial ethics boards (Brock University Health Science Research Ethics Board [REB-23-157] and Newfoundland and Labrador Health Research Ethics Board [HREB 20250577]). All activities will comply with the Tri-Council Policy Statement: Ethical Conduct of Research Involving Humans. Written informed consent will be obtained from all participants. Privacy and confidentiality of participant data or identity will be maintained. Consent forms will be stored separately from deidentified data. Pseudonyms will be used in interview transcripts and any reporting of the results. Participants will be compensated for their participation. Individuals who participate in the program will receive a 1-month free membership to the facility they attend. All client participants will receive a CAD $20 gift card for each of the follow-up appointments that they attend (CAD $40 total), as well as a CAD $30 gift card for each time they get their bloodwork done if they are part of the subsample (CAD $90 total). All participants who participate in an interview or focus group will receive a CAD $30 gift card. This study has been registered at ClinicalTrials.gov. The Standards for Reporting Implementation Studies checklist [93] was used to guide the reporting of this protocol paper and can be found in Multimedia Appendix 1.

## Results

Program implementation within each region is occurring in a phased approach, with partners beginning program delivery in 1 site (2024-2025) before expanding to any additional locations (2025-2027). Program enrollment occurs continuously during the implementation phase across all sites. From May 2024 to November 2025, a total of 13 delivery sites began program delivery (1 regional YMCA decided to launch in 3 sites at once), 722 participants have enrolled in the program, and 406 have begun the program (153/342, 44.7% non-Western or Eastern European, 17/342, 5% of whom report identifying as Indigenous; 80/345, 23.2% men or 82/347, 23.6% male). Further, 334 participants have expressed interest in the substudy, of which 89 have had their first blood draw (19/89, 21.8% identify as a visible minority; 4/89, 5.3% indigenous; 16/82, 19.5% men or 16/81, 19.8% male). An additional 13 sites have confirmed they will launch the program in 2026.

## Discussion

### Principal Findings

This study will provide evidence that SSBC can be scaled up nationwide across community settings to equitably and effectively reduce population-level risk of T2D. Nationwide uptake of DPPs has been previously hindered by the absence of evidence-informed implementation plans tailored to local contexts [38]. This project will identify which implementation strategies work best for whom, where, and how, deepening our understanding of how to translate SSBC to multiple contexts. We move beyond a one-size-fits-all strategy to apply evidence-based implementation principles that will result in equitable program implementation for diverse and priority populations across Canada. This protocol paper documents our key objectives and associated methods for other implementation scientists outside of the realm of T2D prevention to consider when planning to implement evidence-based interventions at scale.

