**Conclusions:**

This study will demonstrate that SSBC can be scaled up nationwide to effectively and equitably reduce the Canadian population-level risk of T2D. This work will determine best practice implementation determinants, outcomes, and strategies critical for sustaining DPP implementation across Canada and beyond. Project findings will be shared with municipality partners and will be copresented with partners and SSBC clients to community organizations, local interested parties, and academics.

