## Methods

### Study Design and Procedures

A hybrid type 2 implementation-effectiveness study design [61] using multiple and mixed methods will be used to evaluate the implementation and effectiveness of SSBC over 6 years (2024-2029). Years 1 and 2 will serve as a planning period (preimplementation phase). Specifically, SSBC will be adapted to the site and local contexts, recruitment and referral plans will be developed, and coaches will be trained to deliver SSBC. Years 2-4 will involve the delivery and monitoring of SSBC in diverse urban Young Men’s Christian Association (YMCA) health and fitness facilities (implementation phase). Individuals who enroll in SSBC will be followed for 24 months after completion of the program (until the end of year 6). Data collected during the implementation phase will be used to guide the cocreation of sustainability models with partner organizations for continued delivery of SSBC in each municipality (sustainability phase in years 5 and 6; see Figure 2 for project timeline).

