#### Objective 1b: Develop an Implementation Strategy Plan and Tracking System

This work will involve developing an implementation strategy plan, or “blueprint,” along with an associated toolkit that formally outlines the strategies for scaling up SSBC across Canada. Implementation strategies are the “methods or techniques used to enhance the adoption, implementation, and sustainability of a program” [43]. The development of this plan will be guided by the identification of barriers and facilitators to SSBC implementation from three sources: (1) findings from the delivery of SSBC at three YMCA facilities in an urban location in BC [50], (2) findings from the delivery of SSBC in five rural locations in BC ([name] et al, unpublished data, 2025), and (3) meetings with the research team and YMCA senior leadership in planning for the urban expansion of SSBC. Barriers and facilitators to implementation identified from the 3 sources will be matched to the Consolidated Framework for Implementation Research (CFIR) [67]. The CFIR–Expert Recommendations for Implementing Change matching tool [68] will be used to identify potential implementation strategies that can be used to address each identified factor. Each implementation strategy will be operationalized for the current context, and information on the actor (ie, who delivers the strategy), temporality (ie, when or at what time), and the targeted implementation outcome will be provided such that this information can be easily used by the delivery sites. This process will provide a rigorous and transparent method for linking implementation barriers and facilitators identified across diverse delivery settings to implementation strategies for use in the current project. Use of implementation strategies will be captured through regular meetings between the research team and each delivery site. Content analysis of regular meeting minutes will be conducted using the FRAME-IS (Framework for Reporting Adaptations and Modifications for Implementation Strategies) [69]. In addition, reasons for implementation strategy adaptation, use, or exclusion will be captured. The integrated findings from objectives 1a and 1b will inform the development of each site’s sustainability planning in Objective 3.

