	**Adaptations**												
		Number and type of adaptations made to the SSBC program before delivery	C, SL, and Y-SL		Adaptation workshop minutes and preimplementation tracking sheets		Extent to which IS was adapted, tailored, refined, or reinvented to meet the needs of organizations at scale-up			C, SL, Y-SL, RRC, and DPRG		Monthly meetings (SL and RRC) and interviews with C, SL, Y-SL, RRC, and DPRG	
		Number and type of adaptations made to the SSBC program during delivery	C, SL, and RRC		Monthly meetings (SL and RRC), and C and SL interviews		Extent to which IS was adapted, tailored, refined, or reinvented to meet the needs of organizations at scale-up			C, SL, Y-SL, RRC, and DPRG		Monthly meetings (SL and RRC), and interviews with C, SL, Y-SL, RRC, and DPRG	
		Number and type of adaptations made to sustain SSBC in years 5 and 6	C, SL, Y-SL, and PP^k^		Focus groups and monthly meetings (SL and RRC)		Extent to which IS was adapted, tailored, refined, or reinvented to meet the needs of organizations at scale-up			C, SL, Y-SL, RRC, and DPRG		Monthly meetings (SL and RRC), and interviews with C, SL, Y-SL, RRC, and DPRG	

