Quantitatively, organizational readiness will be assessed at baseline [70] through surveys with site leads and coaches. Implementer satisfaction with the program will be captured using the Behavioral Interventionist Satisfaction Survey [71] and the Intervention Acceptability, Appropriateness, and Feasibility [72] measures during the delivery process. Client receptivity and satisfaction will be assessed quantitatively using the 8-item Theoretical Framework for Acceptability [73], a 7-item overall program satisfaction measure, and the 1-item net promoter score [74]. In addition, client interviews will be conducted with a purposive subsample (2-3 clients per site) post-SSBC completion to assess client satisfaction and acceptability. Program costs will be captured through monthly invoices and annual reports from sites.

Quantitative data from adoption, reach, dose, fidelity, program cost, and client and coach receptivity measures will be analyzed descriptively. Client demographics will be used to assess representativeness relative to people with prediabetes across Canada. SSBC program sessions will be audio-recorded using tablets with data saved on the University of British Columbia’s secure data research network in real-time; 2 program sessions per year from each coach will be randomly sampled and coded using an abbreviated version of the validated Motivational Interviewing Competency Assessment [75]. Motivational Interviewing Competency Assessment scores will be used to assess coach counseling fidelity, as done previously [57]. All implementation strategies used will be identified and classified according to definitions from the Expert Recommendations for Implementing Change project [76].

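### The article promises to identify which implementation strategies work best, but its methods can only describe how strategies were used and judged, not compare their effects

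*Protocol article*

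**What the plan says.** Three places in the article promise a conclusion about strategies. Principal Findings says "This project will identify which implementation strategies work best for whom, where, and how". The Abstract conclusions say "This work will determine best practice implementation determinants, outcomes, and strategies critical for sustaining DPP implementation". Strengths and Limitations repeats the second claim in almost the same terms.

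The methods say the following.

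- **Design** (Study Design and Procedures): "A hybrid type 2 implementation-effectiveness study design". No assignment, staggering or withholding of strategies is described.
- **Selection** (Objective 1b): barriers and facilitators come from three sources. One is "findings from the delivery of SSBC at three YMCA facilities in an urban location in BC"; the others are five rural BC locations and planning meetings with YMCA senior leadership. A matching tool "will be used to identify potential implementation strategies that can be used to address each identified factor". The result is one blueprint with a toolkit.
- **Site variation** (Objective 1b and Table 1, Adaptations): "reasons for implementation strategy adaptation, use, or exclusion will be captured", and Table 1 records the "Extent to which IS was adapted, tailored, refined, or reinvented to meet the needs of organizations at scale-up".
- **Exposure** (Table 1, Dose delivered): a count of how often strategies are used by the site and by the research team.
- **Analysis** (Objective 2a): "Quantitative data from adoption, reach, dose, fidelity, program cost, and client and coach receptivity measures will be analyzed descriptively". Strategies are identified and classified, and interviews are analysed thematically.
- **Regression** (Objective 2b): the models estimate the effect of SSBC on client outcomes. None concerns strategies.

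**The concern.** To say that one strategy works better than another, or works at all, requires a contrast: sites with and without it, or the same site under different conditions, arranged or adjusted so that the contrast reflects the strategy. The article states the conclusion but describes no such contrast.

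If readers fill the gap by setting strategy use against reach, fidelity or sustainment across sites, they will be comparing sites that differed in their use for reasons of their own. Those reasons (local barriers, staffing, readiness) can also affect the outcome.

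The conclusion would be acted on. Under Objective 3a, data from objectives 1 and 2 go into reports that shape each YMCA's sustainability model. Table 4 tracks which strategies are continued or discontinued, and the Dissemination Plan lists evidence-based guides, decision aids and policy briefs. A strategy could be kept or dropped on an association that says little about its effect.

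**Working it through.** The article gives no effect size, power or sample size for comparing strategies, so there is no figure to reproduce. The check has three steps.

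**1. What the claim needs against what is planned**

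| Needed for a comparative claim | What the article provides |
|---|---|
| Strategy use assigned, or its determinants measured and adjusted for | Use, adaptation or exclusion decided at sites, with reasons recorded |
| A comparison condition for each strategy | None described |
| An analysis linking strategy to outcome | Counts of use, ERIC classification, descriptive outcomes |
| A statement of confounding as a limit | Not in Strengths and Limitations |

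If all sites used the whole blueprint alike, there would be no contrast. If they use it differently, the contrast is self-selected. Neither case supports the claim.

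**2. How far self-selection could move a between-site association (assumed values)**

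With standardised variables, crude slope = true strategy effect + (barrier effect × correlation of use with barriers). Assume a true effect of 0.2 and a barrier effect of -0.5, so crude slope = 0.2 - 0.5r.

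| r | Crude slope |
|---|---|
| +0.7 | 0.2 - 0.35 = -0.15 |
| +0.5 | 0.2 - 0.25 = -0.05 |
| +0.3 | 0.2 - 0.15 = +0.05 |
| 0 | +0.20 |
| -0.3 | 0.2 + 0.15 = +0.35 |
| -0.5 | 0.2 + 0.25 = +0.45 |
| -0.7 | 0.2 + 0.35 = +0.55 |

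Positive r means that sites with more barriers use more strategies; negative r means that better-placed sites use more. The first hides or reverses a benefit (the sign changes above r = 0.2/0.5 = 0.4). The second exaggerates it.

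A simulation with a different model gives the same picture. It used 20,000 runs and 44 sites, the planned total under Organization Implementation Sites. The site outcome was -b × barrier + 0.5 × strategy + noise, with use depending on the barrier through log-odds slope g. All these values are assumptions.

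- g = 0: mean crude contrast +0.50 SD; zero or wrong sign in about 5% of runs.
- g = 1: mean contrast +0.25, +0.09 and -0.08 SD for b = 0.3, 0.5 and 0.7; zero or wrong sign in 21%, 39% and 60% of runs.
- The model is symmetric, so reversing g reverses the bias. For b = 0.5 the bias is 0.09 - 0.50 = -0.41, and g = -1 would give 0.50 + 0.41 = +0.91.

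**3. Precision with no confounding at all**

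For an even split of sites, the difference detectable with 80% power (two-sided 5%) is (1.96 + 0.84) × √(2/n per group).

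- 22 v 22 sites: 2.80 × √(2/22) = 0.84 SD. Power for 0.5 SD is about 38%.
- 13 v 13 sites (Results: 13 begun plus 13 confirmed = 26): 2.80 × √(2/13) = 1.10 SD. Power for 0.5 SD is about 25%.

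**The case against.** The strongest reply has four parts.

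**The wording is discussion prose.** The objective at the end of the Introduction is only to examine implementation, strategies included, and the methods match that. This is true, and it makes the remedy a matter of wording. It does not remove the mismatch, because the abstract and discussion are what many readers will use.

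**An article condenses, so a strategy-outcome analysis may be in the full protocol or the SAP.** That would answer a complaint about missing detail. Here the article itself states both the comparative conclusion and a descriptive analysis, and the two do not fit.

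**Strategy evidence is not only descriptive counts.** This stands. Content analysis of meeting minutes with reasons for use or exclusion, interviews on acceptability, context and feasibility, two-coder thematic analysis, site focus groups and reasons for discontinuing are all planned. They speak to how strategies were used, where, and how they were judged. They also lessen the risk that a useful strategy is dropped without anyone knowing why it was used. They do not estimate comparative effect.

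**No crude between-site slope is planned.** Correct. The calculations show what an inference from such an association would be worth. They do not describe an analysis in the article.

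A reader might go further and infer that strategies are chosen to answer each site's own barriers, so that struggling sites use more and helpful strategies will look useless or harmful. The article does not support this. The blueprint's barriers come from shared sources, and site-level selection enters only later. No section says that sites with more difficulty use more strategies. A site with the staff shortages and turnover noted in Strengths and Limitations might well use fewer, which would inflate the apparent benefit.

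**Conclusion.** The concern holds as a mismatch between claim and method. The article cannot, by its stated methods, identify which strategies work best or establish which are critical for sustaining implementation. It can describe which were used, adapted, continued or dropped, for what reasons, and how delivery teams judged them.

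Any between-site association of strategy use with outcomes may be confounded, in a direction the article does not allow us to predict. The size is unknown: every effect size and correlation in the illustration is assumed. The conclusion rests on the absence of any described contrast, not on those values. The point is confined to claims about strategies and leaves the planned analysis of SSBC's effect on clients untouched.

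**What to change.** Restate the claims in the Abstract conclusions, Principal Findings and Strengths and Limitations; changing only one or two would leave the claim in print. Suggested content: the study will describe which strategies were used, adapted, continued or dropped, for which barriers and in which contexts, and how delivery teams judged them. Add one sentence saying that between-site associations of strategy use with outcomes will not be read as effects of the strategies.

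Optionally, show any between-site summary by baseline organizational readiness, which site leads and coaches already report. This is exploratory and only a partial control, since readiness is one survey construct and not a measure of barrier severity.

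A within-site before-after comparison need not be required. Strategies in place from launch have no earlier period, those started after a poor month bring regression to the mean, and concurrent strategies cannot be separated. Monthly counts may also be small: 722 enrolled and 406 begun over 13 sites and about 19 months is 722/247 = 2.9 and 406/247 = 1.6 per site-month if all sites were open throughout, and more with staggered launch.

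The rewording needs no new data. Its cost is a more modest headline claim.
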